### Study design

This is a two-arm, parallel-group, randomized, double-blind, placebo-controlled, clinical trial and will be carried out at Mofid Children’s Hospital, Tehran, Iran. The study protocol has been developed based on Standard Protocol Items: Recommendations for Interventional Trials (SPIRIT) 2013 checklist (supplemental file 1). Study flow chart of enrolment, allocation, intervention, and assessment and participant timeline are presented in Fig. 1 and Fig. 2, respectively. Written informed consent will be obtained from participants or their legal guardians before participating in the research. This investigation was approved by the Medical Ethics Committee of Iran University of Medical Sciences (IR.IUMS.REC.1400.070) and also registered on the Iranian Registry of Clinical Trials website (identifier: IRCT20210419051010N1). In addition, any amendments to the present study protocol which are related to the safety and/or benefit of patients will require confirmation by the aforementioned departments before the trial is conducted. Any alteration in the study protocol will be sent to the Trials journal.

**Fig. 1 Fig1:**
[figure not shown]
Adapted CONSORT. BMI, body mass index

**Fig. 2 Fig2:**
[figure not shown]
Participant timeline. FMD, flow-mediated dilation; CIMT, carotid intima-media thickness

### Randomization and blinding

After obtaining the informed consent and discussing the objectives of the research, eligible subjects (*n* = 60) will be divided into two equal groups, stratified by sex and the amount of daily insulin intake using stratified block randomization, with 1:1 allocation ratio. The block randomization will be conducted by an assistant and the intervention allocation will be blinded for both the investigators and participants. The sequence of the blocks will be prepared for each stratum using a random numbers table. All patients are randomly allocated to an intervention (Omega-3) group or a placebo group. The manufacturer who is responsible for preparing the supplements will be asked to assign a unique code on the cans containing omega-3 or placebo.

### Intervention

Sixty eligible adolescents with type 1 diabetes will be randomly assigned to the omega-3 (*n* = 30) and placebo groups (*n* = 30). Omega-3 capsules (600 mg) and identical placebo capsules will be respectively taken by patients in the intervention and control group once a day, for 12 weeks. The Karen Pharma & Food Supplement company will provide omega-3 capsules. Omega-3 and placebo capsules will be similar in weight, size, shape, taste, color, and odor. Placebo capsules will be also produced by Karen Pharma & Food Supplement company and contain 600 mg oral glycerin. Naringenin and placebo capsules will be given to the study patients for every one month in study visits. There are four study visits in our trial (before the intervention, after 1 month of intervention, after 2 months of intervention, and at the end of the intervention). Study patients will be informed how to use their supplements, and they will be weekly followed by phone calls. Compliance will be evaluated based on unused supplements by each person. The remaining capsules will be counted to determine total supplement intake. Furthermore, patients will be asked about any adverse events experienced following omega-3 consumption. If the reported adverse events are related to omega-3 consumption, participants will be asked to stop taking supplements, and they will be immediately referred to a specialist for therapy. It should be noted that there will be no dietary recommendation or dietary regimen for study patients.

### Sample size calculation

Considering a type I error of 5%, a power of 90%, and the changes in FMD values as one of the primary outcomes [17], the sample size was computed to be 25 for each study group based on the two-sided t-test. To compensate for an approximate attrition rate of 20% throughout the research, we rise the final sample size to 30 adolescents in each group.

$$ n=\frac{{\left({Z}_{1-\alpha /2}+{Z}_{1-\beta}\right)}^2\times \left({S}_1^2+{S}_2^2\right)}{d^2} $$

(*α* = 5%, 1-β = 90%, *SD*_1_ = 2.7, *SD*_2_ = 2.7, *d* = 2.5)

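### Thirty per group does not cover the stated 20% attrition: 24 would remain, against the 25 computed as needed for 90% power

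*Protocol article*

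**What the plan says.** The Sample size calculation section of the Protocol article sets a type I error of 5%, power of 90%, an SD of 2.7 in each group and a difference of 2.5 in FMD change. It prints the usual formula for comparing two means with normal quantiles and reports that "the sample size was computed to be 25 for each study group based on the two-sided t-test". The next sentence deals with loss: "To compensate for an approximate attrition rate of 20% throughout the research, we rise the final sample size to 30 adolescents in each group". No inflation formula is shown.

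The randomised number is fixed elsewhere. The Intervention section states that "Sixty eligible adolescents with type 1 diabetes will be randomly assigned", 30 to each arm, and the Randomization and blinding section specifies "stratified block randomization, with 1:1 allocation ratio". Nothing else in the article changes the target or gives another basis for 30.

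**The concern.** An attrition allowance should leave the required number of evaluable patients after the assumed loss. The loss is a fraction of those randomised, so the required number is divided by the fraction retained. Multiplying the required number by one plus the attrition rate always gives too few. The step from 25 to 30 is exactly what that multiplication produces at 20%.

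At stake is whether the stated power and the stated attrition allowance agree. A reader of the section would conclude that the trial keeps 90% power for its primary outcome after losing a fifth of its patients. On the section's own inputs it falls slightly below that.

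**Working it through.** **Inputs**, all from the Sample size calculation section: two-sided α = 0.05 (z = 1.960); power 0.90 (z = 1.282); SD = 2.7 in both groups; d = 2.5; attrition 20%; 30 randomised per group. Loss is taken as equal in the two arms.

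**1. Reproduce the plan's 25.**
n = (1.960 + 1.282)² × (2.7² + 2.7²) / 2.5² = 24.51, rounded up to 25. The stated figure reproduces.

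**2. Apply the stated attrition to the stated sample.**
30 × 0.80 = 24 per group (48 in total). This is below 25 and below 24.51, so rounding does not explain the gap.

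**3. How much attrition 30 per group can absorb.**
1 − 25/30 = 5/30 = 16.7%.

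**4. Where 30 may come from.**
- 25 × 1.2 = 30, an exact match.
- 25 / (1 − 0.20) = 31.25, which does not give 30.

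**5. Power at 24 and 25 per group.**
The noncentrality is d / (SD × √(2/n)).
- n = 24: 2.5 / (2.7 × √(2/24)) = 2.5 / 0.779 = 3.207. Normal formula: Φ(3.207 − 1.960) = Φ(1.247) = 89.4%. Two-sided noncentral t on 46 df: 88.1%.
- n = 25: 2.5 / (2.7 × √(2/25)) = 2.5 / 0.764 = 3.274. Normal formula: Φ(1.314) = 90.6%. Noncentral t on 48 df: 89.4%.

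| Per group | Normal formula (printed) | Two-sided t-test (named) |
|---|---|---|
| 24 (20% lost from 30) | 89.4% | 88.1% |
| 25 (stated requirement) | 90.6% | 89.4% |
| 26 | 91.6% | 90.6% |
| 30 (no loss) | 94.8% | 94.1% |

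Against 90%, the shortfall at 24 per group is 90 − 89.4 = 0.6 points by the printed formula and 90 − 88.1 = 1.9 points by the t-test.

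**6. What a full allowance would need.**
The answer depends on the starting figure:
- unrounded 24.51 / 0.80 = 30.64, so 31 per group;
- rounded 25 / 0.80 = 31.25, so 32 per group;
- 26 (the t-test requirement) / 0.80 = 32.5, so 33 per group.

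All three exceed 30.

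**The case against.** The strongest objection is about size. One completer per group is missing, power falls by less than two points on either calculation, and the rate is described only as approximate. No conclusion of the trial would turn on this. That is right about importance, but it does not repair the statement. The sentence names 20% and says that 30 per group compensates for it; an approximate rate may lie above 20% as easily as below.

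A reader might also infer more than the article supports:

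- *That the trial is materially underpowered.* It is not: with 24 per group, power is still 88% to 89% for the planned difference.
- *That the authors demonstrably computed 25 × 1.2.* The article shows no inflation step, so this is inferred from the match. The shortfall holds however 30 was reached.
- *That 32 per group is the one correct number.* It is the result of inflating the rounded 25. Other defensible starting points give 31 or 33.
- *That the mismatch between the normal formula and the named t-test adds to the error.* Planning a t-test with the normal approximation is common and costs one patient per group here (25 against 26). It is a separate matter, and it is the reason power is given on both bases.
- *That withdrawing patients with compliance under 80% (Study population section) erodes the margin further.* Nothing says that these withdrawals fall outside the 20%, which is described as covering the whole study. Counting them again could count the same losses twice. The article gives no attrition rate above 20%.

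**Conclusion.** The statement is wrong as written, and the severity is minor. On the section's own inputs, 30 randomised per group with 20% attrition leaves 24, one fewer than the 25 that the section requires. Power is then 89.4% by the printed formula or 88.1% by the named test, not 90%. The sample as planned supports the stated requirement of 25 only up to 16.7% attrition.

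The power figures assume that the difference of 2.5 and SD of 2.7 apply to the quantity compared, that attrition is equal in the two arms, and that it only reduces numbers without biasing the comparison. The count of 24 needs only the stated rate and the equal split. The finding concerns the agreement of the stated figures; it does not call the design or the choice of 60 patients into question.

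**What to change.** Keep 60 patients and restate the sentence in the Sample size calculation section, for example: *Thirty adolescents per group leave 25 evaluable per group if attrition is at most 16.7%. At 20% attrition, 24 per group remain, and power for a difference of 2.5 with SD 2.7 is about 88% by the two-sided t-test (about 89% by the normal formula shown).*

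This costs one sentence and a slightly less favourable power figure. Recruitment, randomisation and the analysis stay as they are.

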### Outcomes

The primary outcome of the current trial is the alteration in the value of FMD as an endothelial function marker at the end of the trial compared to the baseline value. Alterations in carotid intima-media thickness (CIMT), anthropometric indices including weight, height, and BMI for age *Z*-score, lipid profile including triglyceride (TG), high-density lipoprotein cholesterol (HDL-C), low-density lipoprotein cholesterol (LDL-C), and total cholesterol (TC), glycemic parameters including fasting blood sugar (FBS), hemoglobin A1C (HbA1C), fasting blood insulin (FBI), hemostatic model assessment of insulin resistance (HOMA-IR), and quantitative insulin sensitivity check index (QUICKI), plasma levels of high-sensitivity C-reactive protein (hs-CRP) and erythrocyte sedimentation rate (ESR), blood pressure, BUN, creatinine, proteinuria, energy intake, and consumption of nutrients are considered as secondary outcomes. Furthermore, at the beginning of the research, medical history and demographic factors including age, sex, race, education level, and marital status will be asked from all the patients or their legal guardians.

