## Background

Type 1 diabetes, a chronic disorder characterized by insulin deficiency, is generally thought to be precipitated by an immune-associated destruction of pancreatic β cells [1]. Genetic, environmental, and immunologic factors are involved in the pathogenesis of type 1 diabetes [2, 3]. In genetically susceptible subjects under the triggering impacts of environmental factors, autoimmune destruction of pancreatic β cells occurs, leading to insulin deficiency and, consequently, overt hyperglycemia. Polyuria, thirst, weight loss, and overt hyperglycemia are the most common symptoms of type 1 diabetes and diagnostic markers in adolescents [4, 5]. Compelling evidence indicates that there is a bidirectional correlation between the severity of type 1 diabetes and the probability of occurrence of its complications, including cardiovascular disorders, nephropathy, and neuropathy [6, 7]. Based on the results of a recent meta-analysis, the prevalence and incidence rate of type 1 diabetes were 9.5% and 15 per 100,000 people worldwide, respectively. The global rise in type 1 diabetes faces several challenges including the provision of insulin in underdeveloped and developing countries [8]. The lifetime economic burden of type 1 diabetes places a high disease cost on healthcare systems. Thus, developing novel therapeutic agents for the management of type 1 diabetes and its associated comorbidities is crucial [9].

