## Material and methods

### Study population

Adolescents with type 1 diabetes will be recruited from Mofid Children’s Hospital, Tehran, Iran, by an investigator. The investigator will conduct study assessments and screen study patients. The patients will be diagnosed by a specialist. It should be noted that because of the simultaneous occurrence of the coronavirus disease 2019 (COVID-19) pandemic and implementation of this study, researchers should expand their presence time in Mofid Children’s Hospital for achieving adequate participant enrollment to reach the target sample size. Patients that satisfy the inclusion criteria will be eligible to participate in this research. The inclusion criteria are considered as follows: adolescents aged between 10 to 18 years, whose body mass index (BMI) for age *Z*-score ranges between 5 and 85%, diagnosis of type 1 diabetes by a specialist, receiving insulin therapy, at least 5 years have passed since the diagnosis of type 1 diabetes, and a signed written informed consent form for participation in this trial. The exclusion criteria include subjects who are pregnant or breastfeeding, those affected by endocrine, metabolic, blood clotting, or any acute disorder, and patients who had diabetic ketoacidosis or hypoglycemia (blood sugar level lower than 50 mg/dl) in the last 12 or 3 months, respectively. In addition, subjects who consumed antihypertensive, anti-inflammatory, anticoagulant, lipid-lowering, and weight-lowering agents and antioxidant and omega-3 supplements in the last 6 months prior to the study will be excluded. Patients with fish or seafood allergies and smokers will also be excluded. Participants who are unwilling to continue collaborating on the trial or have poor compliance (less than 80%) with the assigned intervention will be withdrawn from follow-up.

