Blood samples (10 mL) will be drawn following 12-h overnight fasting and centrifuge at 3000 rpm for 5 min to extract serum samples pre-and post-intervention. The concentrations of TC, TG, and HDL-C will be evaluated using commercial kits (DIALAB Inc. kit, Vienna, Austria) before and after the intervention. Serum LDL-C values will be calculated using the Friedewald formula. The concentrations of FBI and FBS will be measured using commercial enzyme-linked immunosorbent assay (ELISA) kit (IBT, USA) and glucose oxidase method, respectively. HbA1c will be assessed using commercial kit (BioRex Inc., Tehran, Iran) by auto-analyzer (Mindray auto hematology analyzer). Moreover, BUN and creatinine will be examined by diacetyl monoxime method and enzymatic method, respectively. ESR will be evaluated by Westergren method using a special tube. In addition, serum hs-CRP levels will be assessed using ELISA kit (Paadco Inc. kit, Tehran, Iran) pre-and post-intervention. Also, the following formulas will be used to determine QUICKI and HOMA-IR. Proteinuria will be evaluated by albumin dipstick through collecting urine samples.

QUICKI: 1/(log (fasting insulin μU/ml) + log (fasting glucose mg/dl))

HOMA-IR: [fasting insulin (μU/ml) × fasting glucose (mg/dl)]/405

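### Fasting insulin, HOMA-IR and QUICKI cannot be read as insulin sensitivity in insulin-treated type 1 diabetes, and daily insulin dose is not a listed outcome

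*Protocol article*

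**What the plan says.** The Background of the protocol article describes the disease as "Type 1 diabetes, a chronic disorder characterized by insulin deficiency" and attributes it to destruction of the beta cells. Under Study population, the inclusion criteria require "receiving insulin therapy, at least 5 years have passed since the diagnosis of type 1 diabetes". No insulin regimen is specified.

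Under Outcomes, the secondary outcomes include fasting insulin, "hemostatic model assessment of insulin resistance (HOMA-IR), and quantitative insulin sensitivity check index (QUICKI"), next to fasting blood sugar and HbA1c. Under Assessment of variables, the blood sample follows a 12-hour fast, insulin is measured by ELISA, and "the following formulas will be used to determine QUICKI and HOMA-IR": "HOMA-IR: [fasting insulin (μU/ml) × fasting glucose (mg/dl)]/405" and "QUICKI: 1/(log (fasting insulin μU/ml) + log (fasting glucose mg/dl")). The assay description names no C-peptide, does not separate injected from endogenous insulin, and gives no condition on the timing of insulin before the sample.

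Insulin dose appears once, under Randomization and blinding, where allocation is "stratified by sex and the amount of daily insulin intake". It is not in the list of outcomes. Under Statistical analysis, the factors named for follow-up during the trial are changes in diet and activity.

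**The concern.** HOMA-IR and QUICKI take a high fasting insulin at a given glucose as a sign of resistance because they suppose that the patient's own pancreas is responding to that glucose. In this population that response is largely absent by the protocol's own definition of the disease. What the assay finds depends largely on what was injected and when, to the extent that the kit detects it.

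The Discussion makes the matter practical. One of the mechanisms it proposes is protection of the liver's sensitivity to insulin, and these indices are the listed outcomes a reader would turn to for evidence of it. If the plan is followed as written, a difference in HOMA-IR or QUICKI would be reported as an effect on sensitivity when it may be nothing of the kind.

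Insulin requirement is a second gap. Over 12 weeks the dose can move, and HbA1c and fasting glucose are easier to interpret when the dose at both ends is known.

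**Working it through.** The plan gives no numerical figure on this point to reproduce, so the check uses its two formulas.

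**Inputs from the documents.** With I for fasting insulin (μU/ml) and G for fasting glucose (mg/dl), from Assessment of variables:
- HOMA-IR = I × G / 405
- QUICKI = 1 / (log I + log G). The base is not stated; base 10 is assumed here.

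**Inputs that are assumptions.** The documents give no expected insulin or glucose values. All values of I and G below are illustrative.

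**Step 1: the two indices carry the same information.** Since log I + log G = log(I × G) and I × G = 405 × HOMA-IR,

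QUICKI = 1 / log10(405 × HOMA-IR).

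Knowing one gives the other exactly, at baseline and at 12 weeks. A rank test on end values gives the same P value for both. Tests on changes may differ slightly because the transform is not linear, but they use no additional data.

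**Step 2: dependence on measured insulin.** HOMA-IR is proportional to I at fixed G. At G = 150:
- I = 10: HOMA-IR = 10 × 150 / 405 = 3.70; QUICKI = 1 / log10(1500) = 0.315
- I = 20: HOMA-IR = 20 × 150 / 405 = 7.41; QUICKI = 1 / log10(3000) = 0.288

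At G = 180, over a wider range of I:

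| I (μU/ml) | HOMA-IR | QUICKI |
|---|---|---|
| 5 | 2.2 | 0.338 |
| 10 | 4.4 | 0.307 |
| 20 | 8.9 | 0.281 |
| 40 | 17.8 | 0.259 |

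These shifts can arise without any change in sensitivity only if the sample is not at steady state, for example because insulin has risen and glucose has not yet fallen. With no stated condition on insulin timing, the protocol article does not rule this out.

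**Step 3: a case where the index does not move.** I = 10 with G = 200, and I = 20 with G = 100, both give I × G = 2000, hence HOMA-IR = 4.94 and QUICKI = 0.303. If extra insulin lowers glucose in proportion, neither index registers it. The indices therefore do not simply follow the dose.

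**Step 4: how much of the outcome list is affected.** The glycaemic outcomes are fasting glucose, HbA1c, fasting insulin, HOMA-IR and QUICKI; three of these five depend on measured insulin. Counted item by item, the secondary list holds 21 entries (energy intake and nutrients counted as one each), so the share is 3 of 21. FMD and its sample-size calculation use none of them.

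**The case against.** The best defence is randomisation. The trial is double-blind and placebo-controlled, and stratified by daily insulin intake, so injection habits should balance between arms in expectation and add noise rather than bias. That stands for the fairness of the comparison. It does not make the index a measure of sensitivity, which is the point here.

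Several stronger readings are tempting, and the documents do not support them.
- *The indices measure only the injected dose.* They also contain glucose, some patients may retain secretion, and the article does not say which insulins the ELISA detects. Step 3 of the working shows a case where dose and index part company. At steady state, doubled insulin with unchanged glucose would itself indicate lower sensitivity.
- *HbA1c cannot be interpreted.* Under blinded randomisation its comparison is a valid total effect, and a systematic difference in titration would itself be a consequence of treatment. What remains is that titration could mask a difference or contribute to one.
- *Testing both indices counts a result twice.* No success rule counts secondary outcomes, so this is redundancy and not an error in a conclusion.
- *Insulin dose is not recorded at 12 weeks.* The article does not show that. The baseline dose must be known for stratification, and the general linear model adjusts for confounders without a closed list. Only its absence as a listed outcome is established.

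**Conclusion.** The concern holds in a limited form. Fasting insulin, HOMA-IR and QUICKI are stated as secondary outcomes in patients who are all insulin-deficient and insulin-treated, and a group difference in them cannot support a conclusion about insulin sensitivity. Because the objection is to outcomes that the article lists and formulas that it defines, a fuller document could not remove it simply by adding analysis detail.

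The conclusion rests on two things: that measured fasting insulin depends largely on injected insulin, which follows from the eligibility criteria but is subject to what the kit detects; and that the sample need not be at steady state. The numerical illustration (HOMA-IR 3.7 versus 7.4) uses assumed values and shows how sensitive the formula is to I; it is not a prediction of what the trial will find.

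The size is moderate: three secondary outcomes lose their intended meaning, and two others (HbA1c and fasting glucose) would be better interpreted beside insulin dose. The primary outcome, its sample size and the main conclusion are untouched.

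**What to change.** 1. Keep fasting insulin, HOMA-IR and QUICKI in the report, but as descriptive measures only. State that no conclusion about insulin sensitivity will be drawn from them, and that QUICKI is a transform of HOMA-IR.
2. Add total daily insulin dose (units/kg/day), recorded at baseline and at the existing 12-week visit, as a secondary outcome, reported alongside HbA1c and fasting glucose. This is a matter of recording only; it asks for no change in anyone's insulin treatment.

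The cost is small. Baseline dose is already needed for stratification, body weight is already measured at both ends, and the final visit already exists, so one data item is added. No new assay is required.

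The downside is that three prespecified secondary outcomes are downgraded after recruitment began on 20 May 2021. The change must be documented as a dated amendment with its reason. A reader might prefer to delete the three measures outright, but removing published outcomes from a running trial invites a charge of selective reporting, and descriptive reporting avoids it.
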